### 2.9 Data analysis

Descriptive statistics measures of mean, standard deviation, median, minimum, maximum, and range will be used to characterize the sample in terms of sociodemographic characteristics and variables of interest for each group in the study. In addition, boxplots will also be created to show these variables in a graphical format. Subsequently, a repeated measures analysis of variance (ANOVA) will be used to identify the differences between the two groups and evaluate which exhibits better outcomes. The assumptions of the ANOVA will be verified through the Mauchly’s test of sphericity, the Levene test for homogeneity of variances and visual observation of the Q-Q plot.

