### 2.4 Sample size calculation

A repeated measures ANOVA with within-between interactions was chosen to evaluate the impact of the treatment on each group relative to their baseline. To achieve 80% power, with an alpha of 0.05, a medium effect size of 0.25, two groups, two measurements per group, a correlation of 0.5 among repeated measures, and a non-sphericity correction of 1, we used GPower v.3.1 (24) to calculate the required sample size, which resulted in 34 subjects per group. Considering a 15% dropout rate, the final sample will consist of 80 individuals (*n* = 40 per group) who meet the inclusion criteria.

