### 2.8 Data collection

We will use the participants’ clinical records to collect the following characteristics: Participants’ sex, age, educational level, occupation, brain tumor history, and comorbidities.

A blinded researcher will assess primary study outcomes at baseline *T0* and after intervention *T1* (until 24 h after the final session).

The following domains will assess the primary outcomes of this study:

The Fiberoptic Endoscopic Evaluation of Swallowing (FEES) will be used alongside the Penetration-Aspiration Scale (PAS). Participants will be asked to swallow solid, semi-liquid, and liquid food. The assessment will be stopped if aspiration occurs, defined as the entry of food into the airway below the true vocal cords (26). The PAS is an 8-point scale that evaluates the severity of food or liquid entering the airway during swallowing, based on FEES observations. It assesses how far the material penetrates and whether it is cleared. Scores range from no airway entry to material entering below the vocal cords, not being cleared, and no protective response (silent aspiration).Gugging Swallowing Test (GUSS). The GUSS is a clinical tool used to assess the safety of swallowing in patients and identify the risk of aspiration. The test evaluates the patient’s ability to swallow different food and liquid consistencies, beginning with thickened fluids and gradually progressing to thin liquids. The GUSS is divided into two main parts: the indirect swallowing test, which assesses the patient’s ability to swallow saliva and checks for symptoms of dysphagia, such as coughing or drooling, and the direct swallowing test, which observes for signs of aspiration or choking as the patient is given substances of increasing difficulty (semisolid, liquid, and solid).

The maximum score indicates safe swallowing without aspiration risk, while lower scores suggest higher aspiration risk.

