Dysphagia Handicap Index (DHI). The DHI is a self-reported questionnaire designed to assess the impact of dysphagia swallowing on an individual’s daily life. It evaluates three key dimensions: physical, functional, and emotional aspects of living with dysphagia. The DHI consists of 25 items, scored using a Likert scale, with higher scores indicating a more significant perceived handicap.Functional Oral Intake Scale (FOIS). The FOIS is a clinical tool used to evaluate a patient’s ability to consume oral foods and liquids. It provides a standardized measure of functional oral intake, particularly in individuals with dysphagia. The scale consists of 7 levels, ranging from complete reliance on non-oral feeding to the ability to eat and drink without restrictions.

The secondary outcome of this study will be evaluated at T1 by the following key domains:

(1)   Recruitment (number of patients that express interest in participating);(2)   Enrollment (number of patients that participate in the program);(3)   Retention (number of sessions and percentage of enrolled participants who completed final program assessments);(4)   Satisfaction (assessed with an exit survey) will be recorded using binary response questions (yes/no) and a 5-point Likert-type scale;(5)   Adverse events that happen throughout the intervention (will be documented in the case report form).

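### The planned repeated measures ANOVA on T0 and T1 is valid, but adjusting T1 for baseline would be more precise at almost no cost, and PAS and FOIS need an ordinal or rank-based analysis beside it

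*Protocol article*

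**What the plan says.** Section 2.9 names one inferential method for the trial: "a repeated measures analysis of variance (ANOVA) will be used to identify the differences between the two groups". It mentions no baseline covariate. The listed assumption checks are Mauchly's "test of sphericity, the Levene test for homogeneity of variances and visual observation" of a Q-Q plot.

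Section 2.4 is more explicit about the tested term: "A repeated measures ANOVA with within-between interactions was chosen to evaluate the impact of the treatment on each group relative to their baseline". It also fixes "a correlation of 0.5 among repeated measures".

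Section 2.8 sets two assessments, T0 and T1, for all four primary outcomes (PAS, GUSS, DHI, FOIS). Two of these are short ordered scales: "The PAS is an 8-point scale that evaluates the severity of food or liquid entering the airway during swallowing", and for FOIS, "The scale consists of 7 levels, ranging from complete reliance on non-oral feeding" up to unrestricted eating and drinking. Section 2.9 applies the same ANOVA to all four.

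**The concern.** In a randomised trial with one baseline and one follow-up measurement, the group-by-time interaction compares mean change between arms. This subtracts the whole baseline value, although T0 predicts T1 only in part. Subtracting too much adds noise. ANCOVA estimates how much of T0 to remove, so its variance is lower whenever the T0–T1 correlation is below 1. T0 is already collected, so the precision is available without new data. In a trial of this size, the loss means wider intervals and lower power for moderate effects.

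Two smaller matters sit in the same section. A mean difference on an 8-category or 7-level ordered scale is hard to interpret, because the steps need not be equally spaced. And sphericity holds by construction with two time points, so Mauchly's test has nothing to test.

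**Working it through.** **Inputs from the protocol article.** Two arms, 1:1 (2.1); T0 and T1 (2.8); correlation ρ = 0.5, alpha 0.05, power 80%, effect size f = 0.25, 34 per group before dropout (2.4). Assumed here: effects of 0.7 and 0.5 SD, values of ρ other than 0.5, and equal SD at T0 and T1.

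**The plan's own figure.** For a 2 × 2 interaction, f = 0.25 is a difference in change of 4f = 1.0 SD. The noncentrality is λ = f² × N × 2/(1 − ρ), with 1 and N − 2 degrees of freedom.
- N = 34 in total: λ = 0.0625 × 34 × 2/0.5 = 8.5, power 0.807.
- N = 68 in total: λ = 17, power 0.982.

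So the stated 34 per group is not reproduced: the inputs give 34 in total. That is a separate point. It matters here because at 34 per group the plan's own effect already has 98% power.

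**Interaction as a change-score test.** With two times, the interaction F is the square of the t statistic on T1 − T0. As a check, for N = 34 (17 per arm) and a 1.0 SD effect, the squared t noncentrality is 17/2 = 8.5, as above.

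**Variance factors, in units of SD².**
- Change score: 2(1 − ρ) = 1.00 at ρ = 0.5.
- ANCOVA: 1 − ρ² = 0.75 at ρ = 0.5.
- Ratio: (1 + ρ)/2 = 0.75. In information terms, 68 patients analysed by ANCOVA act like 68/0.75 = 90.7 analysed by change.
- Over assumed ρ, the ratio is 0.65 at 0.3, 0.85 at 0.7 and 0.95 at 0.9.

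**Power at ρ = 0.5** (noncentral t, two-sided 0.05; 2n − 2 degrees of freedom for change, 2n − 3 for ANCOVA):

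| Evaluable per arm | Effect | Interaction | ANCOVA |
|---|---|---|---|
| 34 | 1.0 SD (plan) | 0.982 | 0.997 |
| 34 | 0.7 SD (assumed) | 0.812 | 0.907 |
| 34 | 0.5 SD (assumed) | 0.529 | 0.650 |
| 26 | 1.0 SD (plan) | 0.942 | 0.983 |
| 26 | 0.7 SD (assumed) | 0.697 | 0.815 |
| 26 | 0.5 SD (assumed) | 0.424 | 0.532 |

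The 26 rows are included because the abstract gives 62 recruited, against 80 in section 2.4: 62 × 0.85 = 52.7, or about 26 per arm.

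At 34 per arm and 80% power, the detectable difference falls from 0.69 to 0.60 SD. For the assumed 0.5 SD effect at 34 per arm, power goes from 0.404 to 0.567 at ρ = 0.3 and from 0.746 to 0.812 at ρ = 0.7.

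**Ordered scales, by illustration only.** A simulated 8-category score was used, with an assumed baseline distribution, general improvement in both arms, latent correlation 0.5, 34 per arm and 4,000 runs per setting:

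| Latent treatment shift | Change score | ANCOVA | Rank ANCOVA |
|---|---|---|---|
| 0 (type I error) | 0.049 | 0.051 | 0.049 |
| 0.5 SD | 0.353 | 0.543 | 0.576 |
| 0.7 SD | 0.541 | 0.812 | 0.838 |

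Error rates are near 5% throughout. Most of the gain comes from baseline adjustment and a little from ranking. With patients moving towards the end of the scale, the change score lost more than normal theory predicts.

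**The case against.** The strongest reply is that nothing in the plan is wrong. Randomisation keeps the interaction test unbiased, its error rate is close to nominal even on an 8-category score, and at the plan's own 1.0 SD effect the gain is only 1.5 percentage points of power (0.982 to 0.997). The larger gains rest on effects that the protocol does not state, on ρ = 0.5, for which it gives no empirical basis, and on a number of evaluable patients that the abstract and section 2.4 leave in conflict. All of this stands, and it makes the point an improvement and not an error.

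A reader might infer from section 2.9 alone that the group main effect will be tested. That term averages T0 with T1 and would halve an effect present only at T1. At 34 per arm and 1.0 SD, the standardised effect would be 0.5/√0.75 = 0.577 and power 0.65. The documents do not support this reading, because section 2.4 names the within-between interaction. At most, section 2.9 should repeat the term.

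A reader might also infer that ANOVA on PAS and FOIS gives false positives. The simulation shows no sign of it, so the issue is mainly what a mean difference means. Section 2.9 also plans medians, ranges and boxplots. A proportional-odds model is not clearly the remedy either: with 7 or 8 levels and about 34 per arm, some categories may be sparse.

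**Conclusion.** The point holds as a nearly free gain in precision. At the protocol's ρ of 0.5, the planned test has 1/0.75 = 1.33 times the variance of ANCOVA, so it needs about a third more patients for the same precision. The direction holds for any ρ below 1, apart from the one degree of freedom spent, and the gain shrinks as ρ rises. In power terms it is negligible at the effect the trial was sized for and useful at smaller effects or with fewer completers. The figures assume equal SD at T0 and T1 and, for the headline, 34 evaluable per arm.

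The PAS and FOIS part is about interpretation first and power second. Mauchly's test is redundant, and removing it changes no result.

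**What to change.** In section 2.9:

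- Make the primary analysis of each outcome an ANCOVA of T1 on group with T0 as covariate, and name the group coefficient, with its 95% CI, as the treatment effect. This also settles which term is tested.
- Keep the group-by-time ANOVA as a sensitivity analysis if wanted.
- For PAS and FOIS, add a baseline-adjusted ordinal or rank-based analysis: rank ANCOVA, or a proportional-odds model if the categories are not too sparse.
- Delete Mauchly's test.

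The cost is one degree of freedom and analysis wording, with no new data. As far as the choice of model goes, the section 2.4 sample size can stay as a conservative figure, with a sentence saying that it was based on the interaction. The conflict over N and the per-group versus total question need their own correction.

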### 2.10 Ethics and dissemination

To ensure ethical compliance, the research will adhere to the Helsinki Declaration (2013 revision) and undergo evaluation by the institution’s Ethics Committee. Before any procedures, participants will receive an informed consent form outlining comprehensive details regarding the study’s objectives, procedures, voluntary participation, and potential risks. Participants will be required to sign the form indicating their agreement.

Researchers will emphasize that participants are free to withdraw their consent at any time without prejudice to future medical care. Participants declining to provide or retracting written informed consent will be excluded or discontinued from the research, but this decision will have no bearing on their ongoing care. During the screening visit, participants will receive a comprehensive explanation of the study’s objectives and the expected level of compliance. Any queries or concerns will be addressed. If participants voluntarily consent to participate, they will be asked to sign two copies of the informed consent form. One copy will be provided to the participant, while the leading researcher will retain the other. Data collection instruments will be encoded using a combination of letters and numbers to ensure participants’ anonymity. The decoder grid will only be accessible to the project manager. All paper and electronic data will be stored in a locked file in a cabinet at Egas Moniz - Cooperativa de Ensino Superior, C.R.L, for a 5-year retention period, after which they will be destroyed.

## 3 Discussion

The results of this randomized controlled trial could have important implications for the management of dysphagia in brain tumor survivors after neurosurgery. Dysphagia is a significant complication following neurosurgical interventions, particularly in brain tumor patients, as it can severely affect nutritional intake, hydration, and overall quality of life (27). If proven effective, Kinesiology taping could offer a novel, non-invasive, and easily applicable therapeutic option that complements existing treatments and enhances rehabilitation outcomes.

Evidence from previous studies suggests that kinesiology taping has beneficial effects on stroke survivors with dysphagia (6, 19), likely due to its impact on neuromuscular function. By providing external support and facilitating proper muscle alignment, kinesiology taping may enhance muscle coordination and proprioception in the muscles involved in swallowing (6, 19). For brain tumor survivors, who often experience post-surgical muscle weakness and impaired neuromuscular control (28), applying kinesiology tape could help improve the biomechanics of swallowing, thereby reducing the risk of aspiration and enhancing safety and efficiency in swallowing.

Additionally, this study addresses a significant gap in literature. Although dysphagia rehabilitation has been studied in stroke patients, few studies have focused on brain tumor survivors despite the high prevalence of swallowing difficulties in this population (8, 29). Brain tumors, especially those in areas responsible for motor control or sensation, can lead to significant neuromuscular impairments (28). Post-surgical dysphagia can further complicate recovery, as these patients often require additional treatments such as radiotherapy or chemotherapy, which can exacerbate swallowing difficulties (30, 31). This trial will be the first to examine kinesiology taping as a rehabilitative intervention for this specific patient population, potentially laying the groundwork for future research.

If kinesiology taping is effective, it could have far-reaching implications for clinical practice. Rehabilitation professionals could incorporate this technique into standard dysphagia care, potentially reducing the need for more invasive interventions. Moreover, since kinesiology taping is relatively inexpensive and non-invasive, it could be particularly beneficial in settings with limited access to specialized rehabilitation services. The ease of application and potential for home use also means that patients could continue their rehabilitation outside the clinical setting, empowering them to take a more active role in their recovery and improving long-term outcomes.

While the results will remain general due to the pilot nature of the study, it is essential to emphasize the importance of developing standardized protocols for managing neurological swallowing disorders (32, 33). Such protocols are fundamental to ensuring consistency and quality of care across different clinical settings. They support the appropriate selection and timing of assessment tools and guide the implementation of evidence-based therapeutic strategies. Moreover, standardized protocols may foster effective interdisciplinary collaboration. This comprehensive approach can enhance diagnostic accuracy, streamline intervention delivery, and improve patient outcomes. Establishing and validating these protocols in populations such as brain tumor survivors is a critical step toward reducing variability in care and optimizing the rehabilitation trajectory for individuals with complex neurological impairments.

### 3.1 Strengths and limitations

Although this randomized controlled trial is the pioneer in exploring the effectiveness of kinesiology taping for treating dysphagia in survivors of brain tumors after undergoing neurosurgical intervention, we have built the protocol based on previous work examining the effectiveness of kinesiology taping on stroke survivors, thus expecting to achieve positive outcomes. In addition, the chosen outcome measures represent those most practically implemented in the clinical settings.

To ensure this randomized controlled trial was designed following trial standards, we used the SPIRIT statement, which is widely endorsed as an international standard for trial protocols, to enhance the quality, transparency, and completeness of trial protocols, which can help to improve the overall reliability and validity of this clinical trial results. Nonetheless, it should be noted that this trial has limitations. First, blinding is essential to minimize bias that can affect study outcomes. In this trial, it is not feasible to blind participants or team members who will implement the intervention. However, to minimize data collection and analysis bias, the research team members responsible for these tasks will be blinded to the treatment allocation, whether the participant received the intervention or the placebo/control. Second, there is no uniform standard care treatment for people with dysphagia in Portugal. For this reason, team members will perform the usual treatment in the Neurosurgery Inpatient Unit, bearing in mind that the time and periodicity of the intervention applied in this trial are possibly more prolonged than the time of rehabilitation care practiced in other similar units. Third, we expect some participants to not complete the intervention due to being transferred to other units or facilities (e.g., rehabilitation units). To minimize the impact of this occurrence on the research results, we assume a dropout rate of 15% when calculating the study’s sample size.

## 4 Conclusion

Kinesiology taping has the potential to be an effective treatment option in brain tumor survivors after undergoing neurosurgery. The study of the effectiveness of new therapeutic approaches in dysphagia care is essential to improve patient outcomes and quality of life. Studying these new approaches can help to identify potential risks and side effects associated with these approaches and determine which approaches are most effective for different populations. Healthcare professionals and researchers should continue exploring new approaches to dysphagia care and study their effectiveness to ensure patients receive the best care.
